#### Control interventions

*Swipe control condition*: In the swipe control condition, participants will use the same app as in the experimental conditions. Here, the app will also provide participants with written instructions but without showing video clips. To approach and avoid the stimuli, participants will be asked to swipe stress-enhancing beliefs away from themselves and stress-reducing beliefs towards themselves on the smartphone screen. After swiping, the app will provide a respective zoom feedback and present a thumbs-up picture (see description of the experimental conditions). In the swipe control condition, the app will not be controlled by an experimenter. The participants will still be observed with an external video camera during the training to keep the conditions between experimental and control intervention equal.*Inactive control condition*: Participants randomized to the inactive control condition will not be invited to the lab and receive any training. They will receive links to the study questionnaires via email and fill them out by themselves.

### Measures

Table 1 gives an overview of all measures taken.

**Table 1 Tab1:** Overview of measures per timepoint

**Variable**	**Instrument**	**Timepoint**^**a**^									
		**T0**	**T1**					**T2**			**T3**
			Pre	Tr1	Post	Tr2	Tr3	Pre	Tr4	Post	
Demographics	Self-devel	x									
Current and past psychotherapy	Self-devel	x									
**Feasibility outcomes**^**b**^											
Intervention usability	Self-devel									x	
App usability	SUS									x	
Acceptability	Self-devel									x	
**Clinical outcomes**											
*Psychometric measures*											
Perceived stress	PSS-10	x	x							x	x
Current stress level	Self-devel		x			x^b^	x^b^	x		x	x
Dysfunctional beliefs	DAS-A/H		x							x	x
Emotional state	Self-devel		x							x	x
Emotion regulation skills	ERSQ		x							x	x
Depressive symptoms	CES-D		x							x	x
*Performance measures*^*b*^											
Reaction time				x		x	x		x		
*N* of failed trials				x		x	x		x		
Felt intensity of emotion	Self-devel			x		x	x		x		
Rating of emotion display	Self-devel			x		x	x		x		
*Physiological measures*^*b*^											
Cortisol (saliva)	Saliva samples		x					x			
α-Amylase (saliva)											
Heart activity	Radar measurement		x		x			x		x	
Respiration											

Note: *Tr* Training, *self-devel* Self-developed questionnaire/item, *PSS-10* Perceived Stress Scale 10, *DAS-A* Dysfunctional Attitude Scale-Agreement, *DAS-H* Dysfunctional Attitude Scale-Helpfulness, *ERSQ* Emotion Regulation Skills Questionnaire, *CES-D* Center for Epidemiological Studies Depression Scale, *SUS* System Usability Scale. ^a^T0, screening; T1, assessment on the first day of training; T2, assessment on the last day of training; T3, assessment 1 week after training completion. At T1 and T2, measures will be taken before (pre) and after (post) the training. Tr1–4 are measures taken during the training after each trial. ^b^Measures are not taken in the inactive control group

#### Feasibility outcomes

With regard to feasibility, we aim to evaluate both the feasibility of the intervention and the possibility of a trial evaluating the efficacy of the intervention.

##### Feasibility of the intervention

Utilizing methods proposed in the context of process evaluation (e.g., Medical Research Council framework [72]), we will evaluate technical problems, adherence, usability, and acceptability. Technical problems will be evaluated by testing whether the proportion of incomplete usages of the intervention due to technical problems is above the a priori set criteria of 95%. Adherence will be evaluated by testing whether the proportion of participants completing the intervention as instructed is above the a priori set criteria of 50%. Usability of the intervention will be assessed with five self-constructed items rated on a 6-point Likert scale (0 to 5). They assess the following aspects of the intervention: comprehensibility of the instructions, viability of emotion expression at the beginning and end of the training, and degree of avoidance of stress-enhancing beliefs and degree of approach towards stress-reducing beliefs with the help of the intervention. In addition, the System Usability Scale (SUS) [73] will be administered in a subset of participants to assess the usability of the AAMT app. The scale consists of ten items measuring the global usability of technological systems on a 5-point Likert scale (1 = *strongly disagree* to 5 = *strongly agree*; exemplary item: “I thought the app was easy to use”). A total score can be obtained by reversely coding five of the ten items, summing them up and multiplying the sum by 2.5. The result is a score ranging from 0 to 100 with a higher score indicating better usability. Two additional items assess the general satisfaction with the app (1) on a 7-point Likert scale from *not at all satisfying* to *exceedingly satisfying* and (2) with school grades. The SUS is a reliable (Cronbach’s alpha = 0.91) and widely applicable measure [74]. Acceptability will be assessed with two self-constructed items. These items will be rated on a 6-point Likert scale (0 to 5). Participants will be asked to rate the helpfulness of the training for the modification of stress-related beliefs and whether they would recommend the training to a friend. The items will be analyzed separately. Additionally, participants will be asked in an open-ended format what they have learned from the training and whether they have general comments or recommendations.

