**Methods:**

We will conduct a parallel randomized controlled pilot study at the Friedrich-Alexander-Universität Erlangen-Nürnberg, Germany. Individuals with elevated stress levels will be randomized to one of eight study conditions (*n* = 10 per condition) — one of six variants of the eAAMT, an active control intervention (swipe-based AAMT), or an inactive control condition. Participants in the intervention groups will engage in four sessions of 20–30 min (e)AAMT training on consecutive days. Participants in the inactive control condition will complete the assessments via an online tool. Non-blinded assessments will be taken directly before and after the training and 1 week after training completion. The primary outcome will be perceived stress. Secondary outcomes will be dysfunctional beliefs, symptoms of depression, emotion regulation skills, and physiological stress measures. We will compute effect sizes and conduct mixed ANOVAs to explore differences in change in outcomes between the eAAMT and control conditions.

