## Methods

### Design

We will conduct a parallel eight-armed randomized controlled pilot study (see Fig. 1 for the study flow and supplemental materials for the spirit checklist of the trial). The study will be conducted at the Department of Clinical Psychology and Psychotherapy of the Friedrich-Alexander-Universität Erlangen-Nürnberg. In the eAAMT and swipe control groups, participants will receive four sessions à 20–30 min of training on four consecutive days, while the inactive control group will not receive any training. Participants will be randomly assigned to one of the eight study groups with a 1:1 allocation. A postdoctoral researcher not otherwise involved in the study will generate a randomization list using random numbers in Microsoft Excel. A block randomization will be performed with a block size of eight. The study is registered in the German Clinical Trials Register (Deutsches Register Klinischer Studien; DRKS00023007).

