### Participants

Inclusion criteria for participation in the pilot study will be the following: (1) heightened levels of perceived stress as indicated by a score of 19 or above on the Perceived Stress Scale-10 (PSS-10; German version: [66]), (2) at least 18 years of age, and (3) ability and willingness to provide informed consent. Following procedures suggested by Heber and colleagues [67], the PSS cut-off score is set at one standard deviation above the PSS mean score in the validation study of the German version of the PSS-10 [66]. Exclusion criteria will be as follows: (1) the presence of a severe psychological condition (i.e., psychosis; based on self-report), (2) physical conditions impairing the expression of emotion (e.g., facial paralysis), (3) heavy smoking (i.e., more than 10 cigarettes/day due to possible confounding influences on cortisol measures), and (4) suicidal ideation. We expect a medium to large effect size based on previous smartphone-based AAMT studies (e.g., [52, 53]). Therefore, we will include *n* = 10 participants per study group (i.e., *N* = 80 in total) as suggested by Bell and colleagues [68] for pilot studies with expected medium to large effect sizes. To complete the intervention per protocol, participants should attend at least three of the four training sessions. To ensure even distribution of subsample sizes across study conditions, we will change randomization block size in case of treatment dropouts. Number of and reasons for dropping out will be recorded and reported for each condition.

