##### Feasibility of the study design

We will collect information on the number of eligible participants and the percentage willing to participate in the study. Moreover, we will report the number of complete follow-up assessments and consider the study as feasible if at least 75% of the assessments will be completed.

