### Statistical analysis plan

Before conducting the analyses, we will test the preconditions and in case of violations use alternative methods. The level of significance will be set to *α* = 0.05. We will report *p*-values for all analyses.

Feasibility outcomes will be analyzed with descriptive statistics and independent *t*-tests to compare the results of the eAAMT conditions with the swipe control condition. To gain insight into the differences in clinical outcome measures between study conditions, we will compute pre-post effect sizes. In addition, we will conduct exploratory analyses using two-way mixed analyses of variance (ANOVAs) with treatment as between-subjects factor and time as within-subjects factor. Because omnibus tests fail to detect differences between single conditions if the majority of conditions do not differ, we plan to run pairwise comparisons comparing the single eAAMT conditions with the inactive control condition and the swipe control condition. In order to prevent alpha-error accumulation, we will first compare the eAAMT conditions to the inactive control condition. Only if the interaction effect in this comparison will be significant, we will also compare the eAAMT conditions to the swipe control condition. Moreover, as this is a pilot trial and we aim to evaluate if the training is effective in itself, we will conduct per protocol analyses. We will also run intention-to-treat analyses to determine the robustness of the results when considering missing data. All analyses will be conducted in R [91] and SPSS.

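### The technical-problems criterion is reversed as written: it asks whether incomplete usages exceed 95%, where the neighbouring criteria count completions

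*Protocol article*

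**What the plan says.** The protocol article sets three numerical feasibility thresholds.

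- **Technical problems** (Feasibility of the intervention): judged by "testing whether the proportion of incomplete usages of the intervention due to technical problems is above the a priori set criteria of 95" per cent.
- **Adherence** (same section, next sentence): "Adherence will be evaluated by testing whether the proportion of participants completing the intervention as instructed is above the a priori set criteria of 50" per cent.
- **Study design** (Feasibility of the study design): the authors will "consider the study as feasible if at least 75% of the assessments will be completed".

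The second and third count something desirable, so a high value is good. The first counts something undesirable, yet keeps the upward direction and a threshold close to 100%. No other part of the article restates or corrects it. The section does not say whether a usage is a session or a participant. The Statistical analysis plan section adds descriptive statistics and t-tests for the feasibility outcomes and a significance level of 0.05, but nothing that changes this criterion.

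**The concern.** Feasibility is the first of the two aims listed under Purpose of the study, and this is one of only three numbers fixed in advance for it. Technical failure is a real possibility: in every emotion-based arm the app is remote-controlled from a tablet over an automatically established wireless link (Experimental interventions).

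The sentence fixes a quantity, a direction and a threshold that do not fit together. Applied literally, it gives a wrong verdict on technical feasibility whichever way the word above is taken. If the authors instead reinterpret it once the data are in, the criterion no longer serves as one set in advance.

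**Working it through.** The 95% is a chosen threshold, so there is no derived figure to reproduce. The check is how the written rule behaves.

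**Step 1. The two readings against the apparent intent.** Let p be the proportion of usages left incomplete because of technical problems. The written rule is p > 0.95. The apparent intent, by analogy with the other two criteria, is 1 - p > 0.95, which is the same as p < 0.05.

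| Observed p | Written rule read as success | Written rule read as problem flag | Apparent intent |
|---|---|---|---|
| below 5% | not met (wrong) | no flag (agrees) | met |
| 5% to 95% | not met (agrees) | no flag (wrong) | not met |
| above 95% | met (wrong) | flag (agrees) | not met |

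Each reading gives wrong verdicts, but over different ranges.

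**Step 2. Size in sessions (illustration).** Inputs: eight conditions with 10 participants each (Abstract, Methods), of which the inactive control receives no training (Design), leaving seven. Trained "participants will receive four sessions" (Design). Assumptions: the session is the unit and attendance is complete.

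- Planned sessions: 7 x 10 x 4 = 280.
- Threshold: 0.95 x 280 = 266, so p > 0.95 needs at least 267 failed sessions.
- Apparent intent, more than 95% complete: at least 267 complete, so at most 280 - 267 = 13 failures. With at least 95% instead, 266 complete suffice and 14 failures are allowed.

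**Step 3. Other units and the word testing.** The protocol does not say whether the observed proportion is simply compared with 95% or tested for significance. For a test I assume a one-sided exact binomial test against 0.95 at the 0.05 level; sidedness is not stated.

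| Denominator | Count needed, simple comparison | Count needed, significance test |
|---|---|---|
| 280 sessions, seven arms | 267 | 273 |
| 240 sessions, six emotion-based arms | 229 | 234 |
| 70 participants, seven arms | 67 | 70 |
| 60 participants, six emotion-based arms | 58 | 60 |

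As written, these are counts of failures. Under the apparent intent they are counts of completions.

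**Step 4. Chance of crossing the line.** With 280 sessions treated as independent (an assumption) and the simple comparison, the binomial probability of 267 or more events is as follows. The protocol gives no expected failure rate, so a range is shown.

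| True failure rate | Written rule crossed | Rule in the apparent direction met |
|---|---|---|
| 1% | effectively 0 | 1.000 |
| 2% | effectively 0 | 0.998 |
| 5% | effectively 0 | 0.462 |
| 10% | effectively 0 | 0.001 |
| 20% | effectively 0 | 0.000 |
| 50% | 4e-63 | 0.000 |
| 80% | 1e-13 | 0.000 |
| 90% | 0.0008 | 0.000 |
| 95% | 0.46 | 0.000 |

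The written rule returns the same answer for an app failing 1% of the time and one failing 80% of the time. With the direction turned round, the same threshold separates low from high failure rates.

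**Step 5. Consistency with adherence.** Under the success reading, at least 267 of 280 sessions are incomplete, leaving at most 13 complete. If completing as instructed means at least three of four sessions (the per-protocol definition under Participants), at most 4 participants could qualify (13 / 3 = 4.3), that is 4 / 70 = 5.7%. The adherence criterion needs more than 50%. The two could not be met together.

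**The case against.** The other side accepts that the sentence is reversed and argues about its weight.

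- **Little hangs on it.** No progression or stopping decision is tied to this threshold. The only explicit rule for calling the study feasible is the 75% assessment-completion rule. Feasibility outcomes are to be described, so readers should see the raw proportion. The adherence criterion would probably expose an app that fails in most sessions, at least if technical failures count as non-completion. The primary outcome, randomisation and efficacy analyses are untouched. This stands and limits the consequence, but it does not make the criterion right.
- **It is an obvious slip that nobody would apply literally.** This is probably so. It is a reason to correct the sentence before analysis, since otherwise the reinterpretation happens after the data are seen.
- **The session counts are not facts of the plan.** This is correct. The unit, the arms counted and full attendance are assumptions, so 267 and 13 are illustrative. The reversal does not depend on them.

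A reader might infer that every failure rate between 5% and 95% is misjudged. That is true only if the sentence is a problem flag. Read as a success rule, it gives the same verdict as the apparent intent in that range and errs below 5% and above 95%. A reader might also infer that the rule cannot tell a working app from a broken one at all. That goes too far: as a problem flag it would still catch failure above 95%, and as a success rule it separates the extremes, only the wrong way round.

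**Conclusion.** The criterion is wrong as written. Whether crossing 95% is meant as success or as a warning, counting incomplete usages and asking for more than 95% gives a wrong verdict over part of the range. As a success rule it rejects a faultless app; as a flag it is silent up to 95% failures. Under the illustrative 280 sessions, the gap is between a line at 267 failures and a tolerance of 13.

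The reversal itself rests on the text alone. That the authors meant more than 95% of usages free of technical interruption is an inference from the adherence and follow-up criteria; the document does not say so. The effect is confined to the technical part of the feasibility aim, where it affects one of three thresholds set in advance.

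**What to change.** Replace the sentence with one that counts the desirable event, for example: technical feasibility is met if the proportion of usages not left incomplete because of a technical problem is above 95% (equivalently, if fewer than 5% are left incomplete for that reason). Keeping above preserves the inequality in the current text; at least 95% would be a small further change and should be a deliberate choice.

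Before analysis, the authors should confirm the intended direction and state whether a usage is a session or a participant. It would help to say at the same time whether the observed proportion is simply compared with 95% or tested, because on the assumed test the tolerance under 280 sessions falls from 13 failures to 280 - 273 = 7. An exact confidence interval for the proportion is optional.

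The cost is one sentence, with no change to data or procedures. The article states that protocol modifications go to the ethics committee and are documented in the trial register (Ethical aspects), so this one should follow that route. Recruitment was still under way when the article was written (Trial status).

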To assess *stress-related (dys-)functional beliefs*, a total of ten items were selected from Rojas and colleagues’ [69] short version of the DAS. The DAS was developed as a self-report instrument to assess dysfunctional attitudes that are typically found in depressive patients. The ten items with the best fit for the stress context of the current study were selected by an expert group under supervision of MB: nine statements consisting of dysfunctional attitudes and one of a functional attitude. Then, two versions of the scale were created. The first version assesses the agreement with the ten DAS items on a 7-point Likert scale (DAS-A; 1 = *fully disagree* to 7 = *fully agree*) and the second version the perceived helpfulness of the beliefs (DAS-H; 1 = *not at all helpful* to 7 = *very helpful*). To obtain a total score, the functional-belief item is reversely coded, and the ten items are summed up. The total score in both versions ranges between 10 and 70. A higher score in the DAS-A represents higher agreement with dysfunctional stress-related beliefs, and a higher score in the DAS-H represents a higher helpfulness rating of dysfunctional beliefs.

To assess the *emotional state*, i.e., the intensity of emotions experienced during the last week, a team of experts in the assessment and regulation of emotions extended the German version of the Positive and Negative Affect Schedule [85] in a way that the following affective states are all assessed with one item: courage, gratitude, joy, pride, excitement, resolve, anger, anxiety, sadness, confidence, disgust, tranquility, love, happiness, relaxation, and content. Each item starts with the instruction “During the last week, I felt…” and invites participants to rate the intensity of the respective emotion during the past week on a 5-point Likert scale ranging from 0 = *not at all* to 4 = *very much*. The items will be analyzed separately.

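### The SUS scoring rule as printed gives 25 to 125, not the stated 0 to 100, because the step that rebases items to 0–4 is missing (minor)

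*Protocol article*

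**What the plan says.** The scale is described in the protocol article under Feasibility of the intervention: "The scale consists of ten items measuring the global usability of technological systems on a 5-point Likert scale", with anchors 1 for strong disagreement and 5 for strong agreement. The scoring rule is "A total score can be obtained by reversely coding five of the ten items, summing them up and multiplying the sum by 2.5". The next sentence gives the range: "The result is a score ranging from 0 to 100 with a higher score indicating better usability".

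The SUS is not given to everyone; it "will be administered in a subset of participants to assess the usability of the AAMT app". Under Statistical analysis plan, feasibility outcomes are to be summarised descriptively and submitted to independent t-tests "to compare the results of the eAAMT conditions with the swipe control condition".

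The article also scores another ten-item instrument in the same way. The two versions of the Dysfunctional Attitude Scale (DAS) have ten items coded 1–7, one of them reversed, which are then summed: "The total score in both versions ranges between 10 and 70".

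**The concern.** Three statements about one instrument stand next to each other: the item coding (1–5), the scoring rule and the resulting range. The rule and coding together fix the range, and it is not the one stated. The article does not merely leave scoring to another document. It prints a specific rule and a specific range, and they disagree.

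At stake is the absolute SUS level. Feasibility is the first aim of this pilot, usability is one of its named components, and descriptive statistics are part of the planned analysis. If the printed rule is coded as it stands, the reported mean is shifted upward by a quarter of the stated scale, and a wholly neutral set of answers looks favourable. The data set is to be made public, so a later user who scores it from this article could make the same mistake.

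**Working it through.** **Inputs, all from the protocol article**

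- Ten SUS items, each coded 1 to 5 (Feasibility of the intervention).
- Five items reversed, then sum, then multiply by 2.5 (same section).
- Stated range 0 to 100 (same section).
- For comparison, DAS: ten items coded 1 to 7, one reversed, summed, stated range 10 to 70 (Clinical outcomes).

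**Step 1: try to reproduce the stated range from the stated rule.** Ordinary reversal of a 1–5 item is 6 − x, which again lies in 1–5.

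- Least favourable answers: sum = 10 × 1 = 10; score = 10 × 2.5 = 25.
- Midpoint on every item: sum = 10 × 3 = 30; score = 30 × 2.5 = 75.
- Most favourable answers: sum = 10 × 5 = 50; score = 50 × 2.5 = 125.

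The rule gives 25–125. The stated 0–100 is not reproduced.

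**Step 2: try another reading of the reversal.** Suppose the five reversed items are recoded as 5 − x (range 0–4) and the other five stay at 1–5.

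- Minimum: (5 × 0 + 5 × 1) × 2.5 = 12.5.
- Maximum: (5 × 4 + 5 × 5) × 2.5 = 112.5.

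This does not give 0–100 either.

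**Step 3: find what does give 0–100.** Working back, 0 / 2.5 = 0 and 100 / 2.5 = 40, so the sum must run from 0 to 40, that is, ten items at 0–4. This means x − 1 for the five direct items and 5 − x for the five reversed ones.

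- Minimum: 0 × 2.5 = 0.
- Midpoint: (10 × 2) × 2.5 = 50.
- Maximum: 40 × 2.5 = 100.

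Equivalently, score = 2.5 × (sum − 10), where the sum is that of the 1–5 items after reversal.

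**Step 4: size of the discrepancy.** Printed rule minus 0–100 score = 2.5 × sum − 2.5 × (sum − 10) = 2.5 × 10 = 25. The difference does not depend on the answers. It was also exactly 25 for every one of 100,000 random response patterns.

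**Step 5: does the article rebase silently elsewhere?** For the DAS, 10 × 1 = 10 and 10 × 7 = 70, which is the stated range. There, items are summed as coded. The article's own convention therefore supports the literal reading of the SUS rule.

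**Step 6: what the shift would reach.**

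- Means: each group mean rises by 25.
- Group comparisons: (mean A + 25) − (mean B + 25) = mean A − mean B. Standard deviations do not change, so t and p do not change.
- Visibility: a printed-rule total exceeds 100 only when the 0–100 score exceeds 100 − 25 = 75. Totals at or below that would look plausible and give no warning.

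**The case against.** The strongest reply is that nothing shows the scores will actually be wrong. The sentence on scoring is a one-line summary of a published instrument, the multiplier of 2.5 and the stated 0–100 range together point to a 0–40 sum, and the likeliest explanation is that the rebasing was intended and dropped from the text. Favourable ratings would also produce totals above 100, which an analyst should notice. This stands in part: the shift is conditional on someone applying the printed rule literally, and no scoring syntax is shown either way. It does not remove the contradiction, because the rule and the range still cannot both be true as printed.

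Two stronger readings are tempting and are not supported:

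- A reader might infer that all usability results are inflated. They are not. Usability of the intervention is also assessed with five self-constructed items rated 0–5, and satisfaction with the app has two separate items. None of these uses the SUS rule, and the SUS itself goes only to a subset.
- A reader might infer that the pilot could wrongly be declared feasible, or that eAAMT could wrongly look more usable than swiping. The article sets numerical criteria for technical problems (95%), adherence (50%) and completed follow-up assessments (75%), but none for the SUS. The comparison with swipe control is invariant to a constant. The primary outcome (PSS-10) and the secondary outcomes do not involve the SUS.

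**Conclusion.** The point holds as an internal contradiction of minor severity. The printed SUS rule yields 25–125 and the stated range is 0–100. If the rule is followed literally, every SUS total is 25 points too high, with an all-midpoint respondent at 75 instead of 50. The exposure is limited to the descriptive SUS level in the subset that completes the scale, and to any reading of that level as a value out of 100. No planned test, feasibility criterion or clinical outcome changes.

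This rests on three assumptions: ordinary reversal (6 − x), all ten items answered, and the same scoring rule applied in every arm. The first affects only the size: reversing as 5 − x, with the other items left as coded, still fails to give 0–100. The third is what makes the shift cancel between groups.

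**What to change.** Replace the scoring sentence with one that includes the missing step: after reverse-coding the five negatively worded items, subtract 1 from each item (0–4), sum the ten items (0–40) and multiply the sum by 2.5 (0–100). Subtracting 10 from the sum before multiplying is the same thing.

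Then check the scoring syntax with three test records: least favourable, all-midpoint and most favourable answers must return 0, 50 and 100. State the same rule in the documentation of the public data set.

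The cost is one sentence and, if the syntax follows the printed rule, one line of code. No data collection, sample size or analysis changes.
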